### Trial design {8}

This study is a parallel-group, two-arm superiority RCT to evaluate the impact of the nutrition therapy Austrian OA Cuisine combined with an evidence-based training programme (GLA:D®) in patients with mild to moderate knee OA in Lower Austria. The treatment combination of the nutrition therapy Austrian OA Cuisine and the GLA:D® training programme is compared with the treatment involving the GLA:D® training programme only.

Participants are informed about all aspects of the study and asked to sign a consent form. Participants are randomised at a 1:1 ratio (see {16a}). Staggered recruitment will be carried out to expand the recruitment phase and to handle all participants’ appointments and trainings more easily.

The duration of the intervention is 9 months. Within this intervention period, the intervention group undergoes the GLA:D® training programme for the first 6 weeks and receives the Austrian OA Cuisine for 9 months. The control group undergoes the GLA:D® training programme for 6 weeks and receives general information regarding a healthy lifestyle. During the 3 months follow-up phase, the intervention group members are expected to implement the Austrian OA Cuisine as well as the exercises of the GLA:D® training programme on their own into their daily life.

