### Outcomes {12}

Data are collected five times over a period of 12 months: at baseline (T0), 6 weeks after the start of the intervention (T1; T0 + 6 weeks), 3 months after the start of the intervention (T2; T0 + 3 months), 9 months after the start of the intervention (T3; T0 + 9 months) and after the follow-up period (T4; T0 + 12 months), including the assessment of blood-based biochemical, anthropometric and behavioural parameters at four data collection points (T0, T2, T3 and T4). The collection of demographic and anamnestic data and the execution of the functional tests take place at all five data collection points.

The primary outcome is the quality of life subscale (QL) of the Knee Injury and Osteoarthritis Outcome Score (KOOS) [62]. The KOOS is used to assess the joint function and patients’ opinion about their knee and associated problems and is a valid and reliable tool compared to others in several studies [62]. The KOOS score for knee-related quality of life (QL) is one of five subscales of the KOOS questionnaire. The QL score is calculated based on four 5-point Likert scale questions, in which each question is assigned a score between 0 and 4. According to the standardised score calculation (www.koos.nu), the mean of the observed items is divided by 4, multiplied by 100 and finally subtracted from 100. A QL score of 100 indicates no symptoms, while a score of 0 means extreme symptoms. The KOOS is valid and reliable and was compared to other instruments in several studies [62].

To evaluate the symptoms of the knee OA and associated problems, the following parameters are analysed:

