## Statistical methods

### Statistical methods for primary and secondary outcomes {20a}

In this study, the focus is on the comparison of data collected at the beginning of the study (T0) and at the end of the study (T4; T0 + 12 months). For all statistical tests, the significance level is set at *p* < 0.05 in accordance with scientific standards. Data are analysed using IBM SPSS Statistics 28 or greater. Normal distribution of metric variables is tested with Shapiro–Wilk-Test and Q-Q-diagrams. For interpreting the results correctly, we also conduct a descriptive analysis showing the arithmetic mean and standard deviation of metric outcome parameters for each group. To control for outliers, we also report the minimum and maximum for each group in addition to a supportive graphical analysis. For interval and nominal scaled variables, we conduct a frequency analysis. To compare the effects of an evidence-based training programme (GLA:D®) with and without the nutrition therapy Austrian OA Cuisine, we conduct an analysis of variance (ANOVA) based on a mixed-linear model of repeated measures looking for assessing effects within each group (e.g. between baseline and the other data collection points) and between groups. In case variables are non-normal or non-metric in scale, we use the Friedman Test, respectively [83]. The group variable (intervention group or control group) serves as the independent variable and the observed outcome parameters (see {12}) serve as the dependent variable.

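### The Friedman fallback for non-normal or non-metric outcomes has no arm term, so those outcomes, possibly including the primary, get no test of diet against control

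*Protocol article*

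**What the plan says.** Trial design {8} describes a "parallel-group, two-arm superiority RCT", and "Participants are randomised at a 1:1 ratio". Both arms receive GLA:D; only the intervention arm receives the nutrition therapy. The question is therefore what the diet adds.

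Statistical methods {20a} gives a default and a fallback. The default is an ANOVA based on a mixed linear model of repeated measures, "looking for assessing effects within each group (e.g. between baseline and the other data collection points) and between groups". Before that comes a distribution check: "Normal distribution of metric variables is tested with Shapiro–Wilk-Test and Q-Q-diagrams". The fallback reads: "In case variables are non-normal or non-metric in scale, we use the Friedman Test, respectively". The next sentence applies to the whole analysis: "The group variable (intervention group or control group) serves as the independent variable".

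The primary outcome is the KOOS quality-of-life subscale. In Outcomes {12}, "The QL score is calculated based on four 5-point Likert scale questions", each scored 0 to 4. The article does not exempt it from the fallback rule, and it names no other method for non-normal or non-metric outcomes.

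**The concern.** The default model can compare the arms. The test that replaces it cannot. The Friedman test is a one-sample procedure for related measurements: it asks whether scores differ between visits in one set of participants. Once an outcome is routed to it, the comparison for which the trial was randomised disappears from the plan.

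This matters more here than in many trials, because both arms get an active programme that the article itself describes (Explanation for the choice of comparators {6b}) as already shown to reduce pain and improve function and quality of life. Change over time is expected in both arms whether or not the diet works, so a significant test of time says nothing about the diet. At stake are the hypotheses on inflammation and oxidative stress, whose markers are plausibly skewed, and possibly the primary hypothesis on quality of life.

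**Working it through.** **1. What the test uses.** With n participants, k visits and R_j the sum over participants of the within-participant rank at visit j, the Friedman statistic (without ties) is

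Q = 12 / [n k (k + 1)] × Σ R_j² − 3 n (k + 1).

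Arm does not appear. Adding a constant to all of one participant's visits leaves that participant's ranks, and hence Q, unchanged.

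**2. Numerical confirmation.** For one simulated data set (50 participants, five visits):
- original data: Q = 6.352, p = 0.174
- participants shuffled across arms: Q = 6.352, p = 0.174
- 30 points added to every visit in one arm: Q = 6.352, p = 0.174

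This result needs no assumption about the trial's data.

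**3. What a pooled Friedman test would report.** From the protocol: SD 15, 25 evaluable or 30 enrolled per arm, five collection points, KOOS-QL scale. Assumed: baseline mean 45, equal correlation between visits, and a gain of 8 points after T0 in both arms.

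Results for 25 per arm, five visits, correlation 0.5 (3,000 runs), as the share of trials with p < 0.05:

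| Scenario | Pooled Friedman | Mann–Whitney on T0–T4 change |
|---|---|---|
| No change in either arm | 5.7% | 5.8% |
| Both arms +8, no diet effect | 94.7% | 5.5% |
| Intervention +8, control −8 | 3.6% | 93.6% |

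The pooled test is nearly always significant when the diet does nothing. It stays near 5% when the arms move apart symmetrically, because the opposite trends cancel.

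For the scenario of both arms +8 with no diet effect, varying the correlation over 0.3–0.7, the visits from two to five and the arm size over 25–30 gives about 75% to over 99%. Two visits are included because the article's focus is T0 against T4; blood markers have four.

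**4. Running Friedman separately in each arm.** In the same scenario (25 per arm, correlation 0.5), exactly one arm is significant in 45.3% of trials. With 30 per arm, the specific pattern of intervention significant and control not occurs in about 18%. Comparing two within-arm p-values is not a between-arm test.

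**5. Could the primary be switched?** With all four items answered, score = 100 − 100 × (item sum / 4) / 4 = 100 − 6.25 × item sum. The sum runs from 0 to 16, so there are 17 possible values in steps of 6.25. Normal data (SD 15) recorded on that grid fail Shapiro–Wilk at 5% in a single check in about:
- 12% of samples of 25
- 14% of samples of 30
- 20% of samples of 50
- 25–29% of samples of 60, across separate simulations

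If any one of several arm-by-visit checks were enough, the rate would be higher, but the article states no such rule.

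**6. Cost of a between-arm rank test.** With 30 per arm, both arms +8 and a further +10 from diet, the rank-sum test on T0–T4 change has about 67–69% power, against 71% for the t-test on change. With 25 per arm the rank-sum figure is about 59%.

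**The case against.** The strongest reply is that the primary method is sound. The default is a mixed model with a between-group comparison, group is named as the independent variable, and the fault sits in one conditional, loosely worded sentence of a condensed article whose analysis plan is not shown. This stands in part: the intent is plainly between-arm, and outcomes that stay with the default are unaffected. But it does not rescue the sentence. The article does not leave the fallback open; it names a specific test that cannot do what the next sentence requires. If Friedman was meant only for the within-group part, no between-arm test is named for these outcomes at all.

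Three stronger readings are tempting, and the documents do not support them.
- **That the trial would answer the diet question falsely in most cases.** The 75% to over 99% is Friedman correctly detecting a real change over time. It becomes a false claim about diet only if someone reads it that way, and the article states no such decision rule. The same holds for the 18% figure. What the text supports is that the question goes unanswered.
- **That KOOS-QL will usually be switched.** Q–Q plots count alongside Shapiro–Wilk. The text does not say whether raw scores, changes or residuals are checked, at which visits, or with the arms pooled. The rates in step 5 are indicative only.
- **That Friedman would drop everyone with a missed visit.** The article plans multiple imputation, under the heading on non-adherence and missing data {20c}, so this does not follow.

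**Conclusion.** The fallback is wrong as written. For every outcome sent to it, the plan provides no test of the intervention against control, in a trial whose stated purpose is that comparison. This follows from the structure of the test and rests on no simulation setting.

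The reach is graded. Non-metric outcomes go to the fallback by rule. Skewed biomarkers such as C-reactive protein and the interleukins plausibly do. The primary outcome possibly does: about 12–29% for a single Shapiro–Wilk check if the underlying scores are normal, with the true rate unknown. The size of the misleading signal, roughly 75% to over 99% for a pooled Friedman test without any diet effect, depends on the assumed 8-point gain in both arms, the correlation of 0.3–0.7 and the number of visits. The direction does not change across that range.

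The sentence should be corrected before the arms are compared, because otherwise the choice between a test that sees the arm and one that does not would depend on the observed data.

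**What to change.** In Statistical methods {20a}, remove the Friedman test as the substitute for the arm comparison and put in its place:
- **Continuous outcomes, including KOOS-QL:** keep the between-arm mixed model, with distributional adequacy judged on residuals and not by a test on the variable itself. Log-transform skewed biomarkers.
- **Where a rank-based or ordinal method is still needed:** name one that compares the arms, for example a Wilcoxon rank-sum test on the T0–T4 change, or an ordinal model with an arm effect. Other between-arm methods would also cure the defect; what matters is that one is named in advance.
- **Friedman:** if kept, label it a descriptive within-arm analysis that carries no conclusion about the diet.

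The cost is a short rewording with no new data. The loss of power is little or none: about 67–69% for the rank-sum test against 71% for the t-test on change under the settings in step 6.

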#### Interim analyses {21b}

There will be no planned interim analysis or stopping guidelines for medical reasons besides the exclusion criteria (see ‘Eligibility criteria {10}’) because no potentially harmful outcomes are expected based on the GLA:D® training programme or the nutrition therapy (see ‘Provisions for post-trial care {30}’).

### Methods for additional analyses (e.g. subgroup analyses) {20b}

Depending on the data and data distribution, subgroup analyses are carried out, e.g. data is clustered according to the body weight. In addition, different correlations - like between the clinical data and the dietary behaviour of the participants - can be analysed.

### Methods in analysis to handle protocol non-adherence and any statistical methods to handle missing data {20c}

Nonadherence data will be analysed by the intention to treat (ITT) method [84]. For handling missing data, multiple imputation will be performed [85].

### Plans to give access to the full protocol, participant-level data and statistical code {31c}

It is not planned to give third parties access, neither to the full protocol, nor the participant data, nor the statistical code. Only the data of the GLA:D® training programme will possibly be used for transnational research in the framework of the GLA:D® International Network in the long term. Therefore, participants sign an additional consent form as described in ‘Additional consent provisions for collection and use of participant data and biological specimens {26b}’.

## Oversight and monitoring

### Composition of the coordinating centre and trial steering committee {5d}

The complexity of OA treatment demands interdisciplinary teams and innovative approaches. The trial steering committee meets these requirements and combines the life sciences of physiotherapy, nutritional sciences, dietetics, human medicine and biomedicine in a unique consortium. Based on their expertise, the study staff members take responsibility for the defined work packages: project management, dissemination, recruitment, physiotherapy, nutritional sciences and dietetics, data collection respectively data processing and analysis.

The trial steering committee meets twice a year. The central study staff members of the St. Pölten University of Applied Sciences meet bi-weekly. The persons responsible for the individual work packages meet as required during the course of the study. The study coordinator has the final responsibility.

### Composition of the data monitoring committee, its role and reporting structure {21a}

A Data Monitoring Committee (DMC) has been established (BW, EH, TA, SC). The DMC ensures correct implementation of the data collection and secure data storage. The collected data are reviewed after each measurement point.

The committee takes all necessary measures for data encryption and for protection of the participants’ data against unauthorised access. If security problems are identified, the Data Monitoring Committee informs the study members and also the funding agency if needed and initiates all necessary steps. In addition, the data protection officer of the study centre can be consulted by the DMC.

### Adverse event reporting and harms {22}

Although the risk of occurring complaints and adverse side effects in this study is considered to be very low, systematic management of side effects is implemented. Participants are advised to report complaints during exercise therapy directly to the physiotherapist, who then forwards this information to the study coordinator. Every potential adverse event is documented in detail and collected at the study centre.

The study coordinator informs the Ethics Committee and the study’s insurance company if necessary.

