**Discussion:**

The prevalence of OA is expected to increase in the future due to ongoing demographic changes and rising obesity rates. The expected results will provide important evidence on whether this interdisciplinary therapeutic approach could be a new, cost-effective and sustainable strategy to address the disease process of OA without negative side effects.

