The GLA:D® training programme consists of two patient education sessions (approx. 1.5 h per session) and two supervised, group-based exercise therapy sessions (approx. 1 h per session) per week over the first 6 weeks of the intervention. The education sessions include information about OA, its symptoms, treatment options and self-management strategies. The group training is based on the NEMEX programme [58] and includes exercises to strengthen hip and knee muscles as well as neuromuscular exercises to improve joint control and stability. Although it is a standardised programme, the exercises can be individualised and adapted to the patients’ needs [13, 59]. The education and training sessions take place at the David Institute Krems and the St. Pölten University of Applied Sciences.

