Besides these measurement appointments, participants take part in monthly 24-h dietary recalls via telephone, except for the first, which is conducted in person at the second measurement point (T1). Interviews are performed by trained project staff in a structured manner based on the framework of the multiple-pass method [74–76]. Except for one 24-h dietary recall, which gathers data on weekend eating behaviour, the other seven 24-h dietary recalls collect data on eating behaviour from Monday to Thursday. To reduce bias, participants know only the calendar week for the 24-h dietary recalls but not the exact day. All 24-h dietary recalls are analysed using the programme nut.s nutritional software (https://www.nutritional-software.at) in its latest version (April 2022) [77].

Furthermore, qualitative data are collected 7 months after each intervention round has started. This will be done via three focus groups with intervention group participants. It will be conducted to analyse the acceptance of the Austrian OA Cuisine and identify perceived social and cultural barriers as well as supportive factors for its integration into daily life. By taking these data into account, a more holistic understanding of the success of the implementation of the nutrition therapy will be possible. Provisional topics used to guide the focus groups will be developed in advance. The focus groups will be managed by a dietitian of the study staff. The dietitian will be responsible for recording, documenting and creating a summary analysis.

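### The harms section specifies a reporting route only for complaints during exercise therapy, and none for the 9-month diet or later unsupervised exercise

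*Protocol article*

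**What the plan says.** Under Adverse event reporting and harms {22}, the protocol article states that "systematic management of side effects is implemented". It then gives one route: "Participants are advised to report complaints during exercise therapy directly to the physiotherapist, who then forwards this information to the study coordinator". A general sentence follows: "Every potential adverse event is documented in detail and collected at the study centre". The study coordinator informs the ethics committee and the insurer where necessary.

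The exercise component is described under Intervention description {11a} as "two supervised, group-based exercise therapy sessions (approx. 1 h per session) per week over the first 6 weeks of the intervention". Under Trial design {8}, "the intervention group undergoes the GLA:D® training programme for the first 6 weeks and receives the Austrian OA Cuisine for 9 months". In the three months after that, the intervention group is to keep up both the diet and the exercises alone.

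The Discussion part of the Abstract says the results will inform whether the approach "could be a new, cost-effective and sustainable strategy to address the disease process of OA without negative side effects".

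**The concern.** A harms record is only as good as the way events come to be known. Here the stated way is passive (the participant must volunteer the complaint), tied to one component (exercise) and addressed to one recipient (the physiotherapist). Both arms receive that component. The component that separates the arms is mainly the diet, and for it the article does not say who asks, when, or who forwards what is heard.

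Two things are at stake. First, a low count of diet-related complaints could reflect how events were collected rather than how well the diet was tolerated. Second, the arms could be compared unfairly: after the group phase, intervention participants speak to a dietitian every month in counselling and control participants do not, so the chance of mentioning a complaint may differ by arm. The direction of that bias is uncertain, because it depends on whether anyone passes such remarks on.

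**Working it through.** The plan states no figure on this point, so there is none to reproduce. The check sets the sections of the protocol article side by side and adds two ratios.

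**1. What the named route covers**
- Supervised exercise lasts 6 weeks (Intervention description {11a}).
- The diet lasts 9 months (Trial design {8}), and 9 × 52/12 = 39 weeks.
- Total follow-up is 12 months, or 52 weeks (Outcomes {12}).
- Share of the diet period: 6/39 = 0.154, about 15%.
- Share of the study: 6/52 = 0.115, about 12%.

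These ratios show how long the route is naturally open. They do not estimate the fraction of events captured. Within the 6 weeks the route is still worded for exercise complaints.

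**2. Other contacts at which an event could surface**

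| Contact | Arm | Timing | Linked to harms reporting? |
|---|---|---|---|
| Individual counselling {11a} | Intervention | Monthly to month 9 | No; the stated purpose is to consolidate knowledge, monitor and motivate |
| 24-h dietary recalls {12} | Not restricted by arm in {12} | Monthly | No |
| Anamnestic data {12}: medical history, joint complaints, sick leave, drugs, self-perceived health and pain | Both | T0 to T4 | No; listed in addition to the outcome parameters |
| Medication and supplement changes {11d} | Both | Data collection points | No |

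None of these sections gives the dietitian, the recall interviewer or the visit staff a duty to elicit or forward adverse events. The listed visit items include no question specific to diet tolerance.

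On the recalls, Outcomes {12} says only that "participants take part in monthly 24-h dietary recalls via telephone, except for the first". The section on strategies to improve adherence {11c} mentions them together with the intervention group's counselling. It should therefore be confirmed that both arms are called before the recalls are relied on as an equal contact.

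**3. What even complete collection could show**

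With zero events among n participants, the one-sided 95% upper limit for the event rate is 1 − 0.05^(1/n).
- n = 30 (planned per arm, Sample size {14}): 1 − 0.05^(1/30) = 0.095, or 9.5%.
- n = 25 (required per arm before the drop-out allowance): 1 − 0.05^(1/25) = 0.113, or 11.3%.

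These limits hold for any arm of that size under any reporting route. They do not measure the gap. They matter only for how a safety statement is worded.

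**The case against.** The strongest reply has four parts.

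- **The general sentence covers everything.** The statement that every potential adverse event is documented is not restricted by component, time or arm. This stands to the extent that nobody can say diet harms go unrecorded. It does not fill the gap, because it describes what happens to an event once known and not how an event outside an exercise session becomes known.
- **Existing visits capture a good deal.** Knee worsening at month 10, for example, would probably show at T4 in joint complaints, pain and the KOOS subscales. This also stands, and it rules out any reading that capture is nil. But these items are not designated as harms data, and diet complaints are reached only indirectly.
- **No safety conclusion is planned.** A reader might infer from the Abstract that the trial expects to conclude there are no negative side effects. The text does not support that: the sentence speaks of evidence on whether this is so. Harms are not among hypotheses H1 to H5 or the listed outcomes. The remark under Interim analyses {21b} that no harm is expected explains the lack of an interim analysis and stopping guidelines; it is not a planned inference.
- **An article condenses a fuller protocol.** Visit forms and staff duties may be set out there. This is a fair limit on confidence. The harms section is not silent, however: it specifies a route and words it for one component only.

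**Conclusion.** The point holds as a specification weakness that is cheap to correct. The article calls its management of side effects systematic, but the only ascertainment route it specifies is spontaneous reporting of exercise complaints, centred on 6 of about 39 diet weeks and 6 of 52 study weeks. For diet-related complaints and for later unsupervised exercise, no route is specified, and the intervention arm's extra counselling allows unequal reporting. The resulting record would be weak evidence on the side-effect question raised in the Abstract.

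Two stronger readings should not be drawn: that diet harms will go wholly unrecorded, and that the trial has committed itself to declaring the approach free of side effects. The general documentation sentence and the visit questions speak against the first, and the Abstract's conditional wording against the second.

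The conclusion assumes that the article's harms section reflects the full procedure. If the full protocol already prescribes active, equal questioning in both arms, the remedy is simply to say so.

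**What to change.** In Adverse event reporting and harms {22}:

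1. Add one question, worded identically in both arms, on any new or worsened complaint of whatever suspected cause, asked at T1, T2, T3 and T4. Ask it at the monthly recall calls too, provided these are made in both arms.
2. Name the role that records and forwards events arising outside exercise sessions.
3. Tabulate events by arm for all randomised participants, including those removed under the attendance rule in {11b}.
4. Limit any safety statement in the results to what this collection supports, and give a confidence limit. With no events in 30 participants, for instance, the statement would carry an upper limit of 9.5%.

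The Abstract puts the end of the intervention at October 2024, so follow-up may already be complete. In that case, tabulate by arm the joint complaints, self-perceived health status, sick leave and medication changes already collected at the visits, and report the limited ascertainment of harms as a limitation.

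The cost is a few minutes per contact, one extra table and a higher recorded event count, since prompted questions bring out more complaints. No new visits are needed.
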